### 7.3 vi. New primary/ secondary cancer

This secondary outcome will be collected at the 3-year follow-up. It is a binary variable and collectively a count/rate (0-n/%). Due to low expected numbers, we do not plan an analysis for this. It will be depicted using survival curves.

## 8. OPERATIVE OUTCOMES

### Operative Outcomes

| #  | Outcome Measures                                    | Control | Intervention | Delta |
|----|-----------------------------------------------------|---------|--------------|-------|
| 4a | vii. Intraoperative blood loss                      |         |              |       |
|    | Count/rate (transfused Y/N)                         | X       | X            | X     |
|    | number of units transfused (including untransfused) | X       | X            | X     |
| 4b | viii. Operative time                                | X       | X            | X     |
| 4c | ix. Conversion to open surgery                      | X       | X            | X     |
| 4d | x. Surgical site infection                          | X       | X            | X     |
| 4e | xi. Stoma rates & complications                     | X       | X            | X     |
| 4f | xii. Radiologically-defined anastomotic leaks       | X       | X            | X     |
| 4g | xiii. Time in intensive care unit                   | X       | X            | X     |
| 4g | xiii. Time in high dependency unit                  | X       | X            | X     |
| 4h | xiv. Re-operation rates                             | X       | X            | X     |
| 4i | xv. Re-admission rates                              | X       | X            | X     |

### 8.1 vii. Intraoperative blood loss

This outcome is reported using two variables: by the presence of intraoperative blood transfusion and by the number of units transfused (including the untransfused). The information to calculate it is derived from the fact of an intraoperative blood transfusion and the number of blood units used. These variables are recorded on the CRF Hospital Stay and Discharge.

The first variable is a binary variable and collectively a count/rate (0-n/%). The second variables are continuous variables and measurements of amount.

### 8.2 viii. Operative time

The information to calculate this outcome is derived from the total time taken for the procedure on the CRF Hospital Stay and Discharge. It is a continuous variable and a measurement of time.

### 8.3 ix. Conversion to open surgery

The information to calculate this outcome is derived from the operation performed as recorded on the CRF Hospital Stay and Discharge. It is a binary variable and collectively a count/rate (0-n/%).

#### 8.4 x. Surgical site infection

The information to calculate this outcome is derived from the complications data on CRF Complications Grading 1 (as derived from previous CRFs eg Hospital Stay and Discharge). It is a binary variable and collectively a count/rate (0-n/%).

#### 8.5 xi. Stoma rates & complications

The information to calculate each of the two subsets of this outcome is derived from the stoma/anastomosis data on the CRFs Hospital Stay and Discharge and Complications Grading 1. The existence of a stoma/anastomosis (Y/N) is derived from the "Stoma/anastomosis formed" CRF elements. The existence of complications (Y/N) is derived from the "Were there any stoma-specific complications?" CRF elements. Each one is a binary variable and collectively a count/rate (0-n/%).

#### 8.6 xii. Radiologically-defined anastomotic leaks

The information to calculate this outcome is derived from the complications data on CRF Complications Grading 1 (as derived from previous CRFs eg Hospital Stay and Discharge). It is a binary variable and collectively a count/rate (0-n/%).

#### 8.7 xiii. Time in intensive care unit and time in high dependency unit

The information to calculate these two lengths of time is derived from the ward and time details on the CRF Hospital Stay and Discharge. Each one is a continuous variable and a measurement of time.

#### 8.8 xiv. Re-operation rates

The information to calculate this outcome is derived from the return to theatre data on the CRFs NBOCA data and Hospital Stay and Discharge. It is a binary variable and collectively a count/rate (0-n/%).

#### 8.9 xv. Re-admission rates

The information to calculate this outcome is derived from the readmission data on the CRF Hospital Stay and Discharge. It is a binary variable and collectively a count/rate (0-n/%).

### 9. HOSPITAL STAY

| #  | Outcome Measures                                    | Control | Intervention | Delta |
|----|-----------------------------------------------------|---------|--------------|-------|
| 5a | xvi. Length of hospital stay (fitness to discharge) | X       | X            | X     |
| 5b | xvii. Days alive and out of hospital                | X       | X            | X     |

### 9.1 xvi. Length of hospital stay (fitness to discharge)

We will calculate the numbers of days of hospital stay using the date of admission and the date of discharge. The information to calculate it is derived from the admission and discharge data on the CRFs Admission and Hospital Stay and Discharge. It is a time-to-event variable and a measurement of time. Instructions for modelling time-to-event variables are given in the appendices.

### 9.2 xvii. Days alive and out of hospital

This secondary outcome is displayed by timepoint. We will calculate the number of days based on the dates of admission, discharge, and 30-day follow-up. The information to calculate it is derived from the discharge and other data on the CRFs Hospital Stay and Discharge and Anthropometry. It is a time-to-event variable and a measurement of time. Instructions for modelling time-to-event variables are given in the appendices.

The possibility of censorship must be noted here.

- If somebody has surgery on the 1st, discharged on the 10th and followed-up on the 30th, then on the 30th the state is known: at that date the days alive and out of hospital is known to be 20 days.
- But if somebody has surgery on the 1st, discharged on the 10th and followed-up on the 27th, then on the 30th the state is not known with certainty as they may have died in the meantime.

To prevent this censorship, we will seek confirmation from the local research teams that the person is still alive on the 30th.

## 10. ANTHROPOMETRY

| #  | Outcome Measures   | Control | Intervention | Delta |
|----|--------------------|---------|--------------|-------|
| 6a | xviii. Weight      | X       | X            | X     |
| 6b | xix. Fat-free mass | X       | X            | X     |

### 10.1 xviii. Weight

This secondary outcome is displayed by timepoint. The information to calculate it is derived from the weight data on the CRFs Anthropometry and Screening Visit. It is a continuous variable and a measurement of mass.

### 10.2 xix. Fat-free mass

This secondary outcome is displayed by timepoint. The information to calculate it is derived from the weight and body fat data on the CRFs Anthropometry and Screening Visit. It is a continuous variable and a measurement of mass. It is reported both as an absolute value (the fat-free mass in kg) and a relative value (the fat-free mass divided by the weight and depicted as a % of body mass).

## 11. FITNESS

| #  | Outcome Measures               | Control | Intervention | Delta |
|----|--------------------------------|---------|--------------|-------|
| 7a | xx. Time for sit-to-stand test | X       | X            | X     |

### 11.1 xx. Time for sit-to-stand test

This secondary outcome is displayed by timepoint. The information to calculate it is derived from the sit-to-stand data on the CRF Sit To Stand Test. It is a continuous variable and a measurement of time.

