### **8.2. Inclusion Criteria**

- Participant is willing and able to give informed consent for participation in the study.
- Able to communicate in English or has a relative/friend/carers acting as interpreter.
- Aged 18 years or above.
- BMI  $\geq 28$  kg/m^2 (or BMI  $\geq 25$  kg/m^2 for people of Black, Asian, or minority ethnic origin).
- Listed for curative elective colorectal resection for cancer.
- If neoadjuvant treatment is indicated, it must have been completed.
- Performance status 0-2.

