#### European Organisation for Research and Treatment of Cancer Quality of Life Questionnaire – Colorectal cancer module (EORTC-QLQ-CR29) – 10 mins

Widely used and validated CRC-specific HRQoL instrument assessing CRC-specific functional status and symptoms post-operatively.

Hospital Anxiety and Depression Scale (HADS) – 5 mins

Widely used and validated anxiety and depression questionnaire.

Resource use questionnaire – 5 mins

A modified Client Service Receipt Inventory [65] will be used to collect data on use of primary care services, social care services, and other health care professional, as well as time off work.

Concomitant medication (5 min)

Participants will be asked to bring their prescription or a list of their medication at the screening visit for these to be recorded.

Weight and body composition – 3 mins

Weight will be measured barefoot and with light clothing to the nearest 0.1kg using a calibrated digital scale which will also estimate body composition using bioelectrical impedance.

Height – 2 mins

Height without shoes will be measured to the nearest 0.1cm using a stadiometer.

5 times sit to stand test – 3 mins

Participants sit in a standard straight-backed stable chair (without wheels) positioned by a wall. They then stand fully and sit back down, without using the hands, five times, as quickly as possible.

Post-operative complications

Presence and type of any morbidity. This will be based on medical records for complications during the hospital stay and on participants reporting it using a standard proforma for complications following discharge. They will be graded (as I-V) independently by two researchers blinded to treatment allocation with the Clavien-Dindo classification of post-operative complications, the most widely used and validated measure.[66]

Table 1: Clavien-Dindo classification of post-operative complications

| Morbidity grade definition |                                                                                                                                                                                                                                                                                                                                                             |

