### **11.8. Procedure for Accounting for Missing, Unused, and Spurious Data.**

Missing data will be imputed using appropriate methodology, as detailed in the SAP.

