| 7. Fitness                             | xx. Time for sit-to-stand test                                | xx: Baseline, 30 days post-op                                        | Continuous                      | See lookup    |            |
| 8. HRQoL                               | xxi. EQ-5D-5L (Index score)                                   | xxi-xxii: Baseline, pre-operative assessment 3 and 30 days post-op   | Continuous                      | See lookup    |            |
|                                        | xxi. EQ-5D-5L (VAS)                                           | ditto                                                                | Continuous                      | See lookup    |            |
|                                        | xxii. HADS (anxiety) continuous                               | ditto                                                                | Continuous                      | See lookup    |            |
|                                        | xxii. HADS (depression) continuous                            | ditto                                                                | Continuous                      | See lookup    |            |
|                                        | xxiii. EORTC-QLQ-CR29                                         |                                                                      |                                 |               |            |
|                                        | 29 individual items                                           | ditto                                                                | N/A: not model                  |               |            |
| 9. Costs & resource use                | N/A - dealt with by health economics                          |                                                                      |                                 |               |            |
| 10. Adverse events                     | xxvii. Adverse events (excluding morbidity i-vi)              | xxvii: Baseline, pre-operative assessment and 30 days post-op        | N/A: not model                  |               |            |

Details of each variable are provided below.

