## 15. FURTHER CONSIDERATIONS ON THE ANALYTICAL APPROACH

### 15.1 Missing data

Missing data will be checked and either corrected if wrong or left if legitimate. Missing data will not be imputed (but see sensitivity analysis). The amount of missing data will be quantified and analyses for variables with missing data will be noted as such.

Mixed effects models usually do not require imputation as they are usually robust to missing data (although this depends if missing data is missing at random or not).

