## 15.4 Sensitivity Analyses

Sensitivity analyses will be done on at least the following:

- **Per-protocol analysis.** The per-protocol analysis will repeat the above models using the per protocol population as defined in section 3.
- **Stratification factors.** The two stratification factors are performance status (“0” vs “1-2”) and age at diagnosis (“< 70 years” and “ $\geq$ 70 years”). For sensitivity analysis we will do the following:
  - Repeat the models with an interaction term between age at diagnosis (“< 70 years” and “ $\geq$ 70 years”) and treatment. This will be expanded to “...and treatment and time” if time is an input variable, see below.
  - Repeat the models with an interaction term between performance status (“0” vs “1-2”) and treatment. This will be expanded to “...and treatment and time” if time is an input variable, see below.
  - Models measuring the state at one timepoint (eg discharge) or the state change between two timepoints will not need a time variable. Models measuring the state at two or more timepoints (eg baseline vs admission vs 30-days post-op) will need a time variable. In such cases, the interaction above will include the time variable. The paper at [7] is an example of this.
- **Other.** Other sensitivity analyses may be conducted if deemed necessary by the Trial Statistician.

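### Sit-to-stand is analysed only as a completion time without imputation, so a failed attempt has no value and the worst result goes uncounted; effects in either direction may be pulled toward zero

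*Combined protocol and SAP*

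**What the plan says.** Protocol 9.6.4 describes the test: "They then stand fully and sit back down, without using the hands, five times, as quickly as possible". It gives no time limit and no rule for an attempt that fails.

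The supplement's table of secondary outcomes types the result as continuous, with timepoints "xx: Baseline, 30 days post-op", so there is one follow-up value. Supplement 11.1 takes the data from the sit-to-stand CRF and adds: "It is a continuous variable and a measurement of time".

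On missing values, supplement 15.1 says: "Missing data will not be imputed (but see sensitivity analysis"). It also says the amount of missing data will be quantified and the affected analyses flagged. Its justification is: "Mixed effects models usually do not require imputation as they are usually robust to missing data", with an added caveat that this depends on whether the data are missing at random.

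The sensitivity analyses in supplement 15.4 are a per-protocol analysis and interactions with the two stratification factors. Beyond those: "Other sensitivity analyses may be conducted if deemed necessary by the Trial Statistician".

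Protocol 11.8 points the other way: "Missing data will be imputed using appropriate methodology, as detailed in the SAP". SAP 6.3 sets out missing-data rules only for the progression criteria.

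**The concern.** Failing to complete five stands is a result, and it is the worst one the test can give. A plan that holds only a time in seconds has nowhere to put it. The failed attempt then looks the same as a visit that never took place, and neither is imputed.

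Sit-to-stand is the only outcome listed under fitness. Improved physical function is part of the trial's rationale, and the protocol's background acknowledges a theoretical worry about muscle loss. The single follow-up is about 30 days after bowel resection, a time when inability is plausible. With 36 per arm, each person unable is 1/36 = 2.8% of an arm. An arm with more people unable could show a better mean time because its weakest members have no time to contribute. The definition could also carry over into the definitive trial.

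**Working it through.** The plan gives no figure for this outcome, so there is none to reproduce. The check has two parts: what the text does to a failed attempt, and how large the effect could be on assumed values.

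**1. The text applied to three records at 30 days**

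Take 12 s, 18 s and 'unable'. Supplement 11.1 admits only a time and 15.1 does not impute, so the mean is (12 + 18)/2 = 15 s from two people. That one of three failed the test does not appear in the result.

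**2. Completer means, closed form (all inputs assumed)**

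Times are log-normal with median 13 s and log-SD s = 0.35. A participant is unable if their time would exceed a cut-off c.

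- Mean of all: 13 × exp(0.35²/2) = 13.82 s.
- Completer mean: 13.82 × Φ(z − s)/Φ(z), where z = ln(c/13)/s.
- 5% unable, z = 1.645: 13.82 × 0.9023/0.95 = 13.13 s.
- 10% unable, z = 1.282: 13.82 × 0.8242/0.90 = 12.66 s.
- 20% unable, z = 0.842: 13.82 × 0.6885/0.80 = 11.90 s.

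Now let the diet shorten every time by 15%. The true difference is −0.15 × 13.82 = −2.07 s. With the same cut-off, z in the treated arm rises by −ln(0.85)/0.35 = 0.464. With 10% of controls unable, 4.0% of the treated arm are unable. Their completer mean is 11.75 × 0.9186/0.9596 = 11.25 s, and the difference is 11.25 − 12.66 = −1.41 s, which is 32% too small. With 20% of controls unable it is −1.11 s, 46% too small.

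**3. The same model with the planned baseline adjustment**

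Those are unadjusted means, whereas the plan adjusts for baseline. Regressing the 30-day time on arm and baseline among completers, with an assumed correlation of 0.6 to 0.8, gives by simulation:

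| Controls unable | Shortfall in a true −2.07 s | Estimate |
|---|---|---|
| 2% | about 6-9% | −1.95 to −1.88 s |
| 10% | about 19-25% | −1.68 to −1.55 s |
| 20% | about 29-39% | −1.47 to −1.26 s |

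**4. A second assumed model, to test direction and model choice**

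Times are normal with mean 13 s, SD 4 s and correlation 0.6. Controls truly slow by 2.0 s, and inability means a 30-day time above 22, 20 or 18 s.

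| Quantity | Truth | 4% of controls unable | 11% | 23% |
|---|---|---|---|---|
| Control slowing, completers | 2.0 | 1.86 | 1.67 | 1.38 |
| Control slowing, mixed model under missing at random | 2.0 | 1.76 | 1.41 | 0.81 |
| Benefit, baseline-adjusted completers | 2.0 | 1.84 | 1.68 | 1.44 |
| Benefit, mixed model | 2.0 | 1.84 | 1.67 | 1.40 |
| Harm, baseline-adjusted completers | 2.0 | 1.68 | 1.45 | 1.20 |
| Harm, mixed model | 2.0 | 1.66 | 1.40 | 1.10 |

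Benefit and harm both shrink, by 8% (1.84 against 2.0) up to 45% (1.10 against 2.0). With no true effect and equal inability the difference stays at zero. A median that ranks 'unable' as worst returns 2.0 s in every non-null case, to within 0.02 s; no more than 40% of an arm was unable in any of them.

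**5. When there is no bias**

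If inability is unrelated to the time a participant would have had, the difference in times is unbiased. For example, 10% against 5% unable at random leaves 32.4 and 34.2 completers per 36 and the same expected difference. Only the information on who was unable is lost.

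**The case against.** The case against has real substance.

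- **Direction.** A reader might infer that any benefit of the diet must be understated. The documents do not support that. It needs a true benefit and inability that follows poor function. If the diet caused more inability, harm would be masked instead.
- **Leaving the model.** A reader might also infer that a participant unable at 30 days drops out of the analysis altogether. That holds if baseline is a covariate. Supplement 4.1 also allows a time-point term and a participant random effect. If baseline is modelled as a timepoint, the participant stays in through that value, although the bias remains.
- **Documents not shown.** The sit-to-stand CRF and the Data Definitions and Tables document cited in the SAP introduction may already hold an 'unable' code. The gap shown here is in the analysis plan.
- **Supplement 15.1.** It states the missing-at-random caveat itself and promises to quantify missing data. But a count of missing values does not separate failed attempts from missed visits, and the discretionary clause in 15.4 commits to nothing.
- **Size.** Entry requires "Performance status 0-2", which may keep inability rare. The sharp cut-off, with everyone unable slower than every completer, is an assumption. The 32-46% shortfall applies only to unadjusted means.
- **Importance.** Fat-free mass addresses muscle loss directly and EQ-5D-5L covers mobility. No p-values are reported, and the outcome is outside the progression rule.

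These points limit direction, size and importance. They do not supply a rule for a failed attempt.

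**Conclusion.** The concern holds in a limited form. As written, the supplement gives no value to a participant who attempts five stands and fails, does not impute one, and names no analysis that would count the failure. Its appeal to mixed models rests on missing at random, which is doubtful here. Protocol 11.8 and supplement 15.1 also contradict each other on imputation for this outcome.

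If inability tracks poor function, post-operative fitness loss is understated and a between-arm difference in either direction is typically pulled toward zero. The true size cannot be stated, because the documents give no mean, SD or inability rate. The baseline-adjusted illustration ranges from about 6-9% too small with 2% of controls unable to 29-39% with 20%. It rests wholly on the assumed distribution, the 0.6-0.8 correlation and the sharp cut-off. If inability is unrelated to function, the difference in times is not biased.

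No trial decision turns on this. It is a modest but specific improvement to a descriptive secondary outcome.

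**What to change.** In supplement 11.1:

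1. Separate 'attempted, unable to complete five stands without hands' from 'test not done', using the CRF field if one exists.
2. Report the count and percentage unable by arm and visit, beside the completion time.
3. Keep the baseline-adjusted time in seconds, labelled as a description of completers. Its SD remains useful for planning the definitive trial.
4. Add one supplementary between-arm comparison that counts inability: rank 'unable' as worst, treat it as right-censored beyond the slowest completer, or compare medians with 'unable' placed last.

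Separately, reconcile protocol 11.8 with supplement 15.1 so that one rule on imputation governs the secondary outcomes.

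The cost is one extra table row, one extra analysis and at most one CRF field. The rank comparison does not give an effect in seconds, which is why it should sit beside the completer time and not replace it.
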